## Abstract

**Background:**

Approximately 20%-25% of patients with metastatic castration-resistant prostate cancer (mCRPC) harbor a deleterious germline or somatic mutation in the homologous recombination repair (HRR) pathway genes, which is involved in the repair of double-stranded DNA damage. Half of these mutations are germline, while the remaining are exclusively somatic. While polyadenosine 5’diphosphoribose [poly (ADP-ribose)] polymerase inhibitors, such as olaparib and rucaparib, are effective in this subgroup, their widespread use is limited due to the associated high cost, especially in resource-constrained settings. Notably, platinum agents like carboplatin have exquisite sensitivity to cells with defective DNA repair machinery. Carboplatin, a conventional, inexpensive chemotherapeutic agent, offers a potential alternative treatment in such patients. Several retrospective small case series support this hypothesis. However, there are no prospective clinical trials of carboplatin in patients with mCRPC with HRR mutations.

**Objective:**

The primary objective is to assess the objective response rate of 3 weekly carboplatin treatments in patients with mCRPC harboring deleterious mutations in the HRR pathway genes and previously treated with a taxane or a novel antiandrogen agent. The secondary objectives include progression-free survival, health-related quality of life, and safety profile of carboplatin.

**Methods:**

Patients diagnosed with mCRPC harboring HRR pathway mutations previously treated with docetaxel or novel antiandrogen agents (abiraterone, enzalutamide, apalutamide, or darolutamide) or both will be eligible. Genes involved directly or indirectly in the HRR pathway will be tested. In this single-arm phase II study, we will screen approximately 200 patients to enroll 49 patients, and carboplatin (dosing at the area under curve=5) will be administered every 3 weeks until progression or intolerable side effects. The primary end point will be assessed as the proportion of patients with a reduction of serum prostate-specific antigen by more than 50% from enrollment. Secondary outcomes include progression-free survival—soft-tissue disease progression (by response evaluation criteria in solid tumors, version 1.1, and bone lesion progression using Prostate Cancer Clinical Trials Working Group 3 criteria), health-related quality of life during carboplatin treatment using the Functional Assessment of Cancer Therapy—Prostate questionnaire and the European Organisation for Research and Treatment of Cancer questionnaire and safety profile of carboplatin (National Cancer Institute’s Common Terminology Criteria for Adverse Events version 5.0).

**Results:**

The trial started enrollment in September 2023. This trial is ongoing, and 12 patients have been recruited to date. All 49 participants will be enrolled according to plan.

**Conclusions:**

This prospective phase II trial represents a critical step toward addressing the therapeutic gap in patients with mCRPC harboring HRR pathway mutations, particularly in demographic regions with limited access to poly (ADP-ribose) polymerase inhibitors. Outcomes from this study will inform clinical practice and guide future phase III randomized trials, ultimately improving patient outcomes globally.

**Trial Registration:**

Clinical Trials Registry of India CTRI/2023/04/051507; https://ctri.nic.in/Clinicaltrials/pmaindet2.php?EncHid=Njc0NjU=&Enc=&userName=

**International Registered Report Identifier (IRRID):**

DERR1-10.2196/54086

## Introduction

Patients with metastatic prostate cancer are treated with androgen deprivation therapy, chemotherapeutic agents, or novel antiandrogen agents [1]. These patients eventually develop resistance to androgen deprivation therapy, and this state, known as castration-resistant prostate cancer, is incurable despite the advent of several newer therapies [2]. The therapeutic landscape for metastatic castration-resistant prostate cancer (mCRPC) includes chemotherapeutic agents, novel antiandrogen agents, and radioligand therapies [3].

Pritchard et al [4] reported that 11.8% of men with metastatic prostate cancer harbor deleterious germline mutations, primarily in *BRCA2*, followed by *ATM*, *CHEK2*, *BRCA1*, *RAD51D*, and *PALB41* genes. Subsequent studies evaluated the prevalence of deleterious somatic mutations within the homologous recombination repair (HRR) pathway in 25%-30% of patients with mCRPC [5]. Polyadenosine 5’diphosphoribose (poly [ADP-ribose]) polymerase inhibitor (PARP) inhibitors employ a strategy of synthetic lethality, inhibiting the base excision repair pathway, leading to the accumulation of unrepaired DNA breaks within HRR-deficient tumor cells, culminating in cancer cell death [6-8]. Olaparib, a PARP inhibitor, demonstrated an impressive 88% response rate in patients with mCRPC with HRR gene abnormalities, in contrast to a minimal 3% response in those without these mutations [9,10]. The pivotal PROfound trial supported these findings, leading to Food and Drug Administration approval for patients with mCRPC harboring HRR gene mutations [5]. Similar efficacy was observed with other PARP inhibitors, including rucaparib and talazoparib [11,12]. However, most patients with mCRPC harboring HRR gene mutations residing in low- and middle-income countries do not have access to PARP inhibitors due to the high cost.

Interestingly, HRR-deficient tumors also exhibit increased sensitivity to platinum chemotherapeutic agents (eg, carboplatin) due to their reliance on the HRR pathway for DNA double-strand break repair. This vulnerability has been exploited by platinum-containing treatments in breast and ovarian tumors [13,14]. Initial retrospective studies involving carboplatin in unselected patients with mCRPC showed encouraging efficacy, particularly within the subset carrying HRR gene alterations [15-17]. However, these studies are limited by several biases.

Despite a strong scientific rationale and encouraging preliminary data from real-world studies, no prospective study has been reported to assess the role of carboplatin in this subset of patients. Therefore, we planned this phase II single-arm study to evaluate the efficacy of carboplatin in patients with metastatic prostate cancer harboring mutations in the HRR pathway.

## Methods

### Objectives

This study is an investigator-initiated, prospective phase II, single-arm clinical trial. The primary objective of this study is to assess the prostate-specific antigen (PSA) response rate of 3 weekly carboplatin (dose at area under the curve 5) in patients with mCRPC harboring deleterious or likely deleterious mutations in the HRR genes and previously treated with a taxane or a novel antiandrogen (proportion of patients with more than 50% serum PSA decline).

The secondary objectives are to compare the effect of oral gabapentin with placebo on the following:

Progression-free survival—soft-tissue disease progression (by response evaluation criteria in solid tumors, version 1.1) and bone lesion progression (by Prostate Cancer Clinical Trials Working Group 3 criteria)Health-related quality of life during carboplatin treatment (Functional Assessment of Cancer Therapy—Prostate questionnaire and European Organisation for Research and Treatment of Cancer questionnaire)The safety profile of carboplatin (National Cancer Institute’s Common Terminology Criteria for Adverse Events, version 5.0)

### Study Setting

This study is being conducted in the outpatient department of [name] Institute Rotary Cancer Hospital, New Delhi, India, and the National Cancer Institute, Jhajjar, the 2 cancer blocks of the All India Institute of Medical Sciences, New Delhi, a central government-funded tertiary care teaching hospital. The catchment area includes an over 20 million population from the Northern states of India, with approximately 15,000 patients with cancer being treated every year.

### Eligibility Criteria

All the following criteria must be met for enrollment:

Histological diagnosis of prostate cancer.Serum testosterone <50 ng/dL within 28 days before screening.Documented current evidence of mCRPC, where metastatic status is defined as at least one documented metastatic lesion on either a bone scan, computed tomography, or magnetic resonance imaging scan.Prior treatment with docetaxel or at least one of the novel antiandrogen agents (abiraterone, enzalutamide, apalutamide, or darolutamide) or both.Mutation (germline or somatic) in the HRR pathway in either blood or biopsy samples.Written informed consent to participate.Eastern Cooperative Oncology Group performance status of 0-1.Aged older than 18 years.Adequate organ function:Absolute neutrophil count ≥1.5 × 109/LHemoglobin ≥10.0 g/dL with no blood transfusions in the past 28 days.Platelet count ≥100 × 109/L.Total bilirubin ≤1.5 × institutional upper limit of normal (ULN).Aspartate aminotransferase (serum glutamic oxaloacetic transaminase) or alanine aminotransferase (serum glutamic pyruvate transaminase) ≤2.5 × institutional ULN unless liver metastases are present in which case, they must be ≤5 × ULN.Subjects must have an estimated creatinine clearance using the Cockcroft-Gault equation for men of ≥40 mL/minute.

Patients with any of the following will be excluded from the trial:

Patients with symptomatic brain metastases. A scan to confirm the absence of brain metastases is unnecessary in all patients.
Patients with spinal cord compression, unless considered to have received definitive treatment for this and evidence of clinically stable disease for 28 days.Patients are considered as poor medical risk due to a serious, uncontrolled medical disorder, nonmalignant systemic disease, or active, uncontrolled infection. Examples include but are not limited to uncontrolled ventricular arrhythmia, recent (within 3 months) myocardial infarction, uncontrolled major seizure disorder, unstable spinal cord compression, superior vena cava syndrome, extensive interstitial bilateral lung disease on high-resolution computed tomography scan, or any psychiatric disorder that prohibits obtaining informed consent.Patients with a known hypersensitivity to carboplatin.

One of this study’s investigators will obtain written informed consent from every patient before enrollment, during which the benefits and risks of participation will be informed in the local language (Hindi or English) that the patient comprehends. The study consists of two parts: (1) screening of tumor tissue or blood for mutations in the HRR pathway and (2) administration of carboplatin in patients found to harbor a deleterious or likely deleterious mutation in the HRR pathway.

Screening of mutations in the HRR pathway will be performed in the tumor tissue for the HRR genes using next-generation sequencing. The initial archived biopsy sample will be retrieved after informed consent is obtained. In patients where the initial biopsy sample is inaccessible or deemed to be of inadequate quality for next-generation sequencing, blood samples will be sent to assess germline mutations in the HRR pathway.

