### Statistical Methods

The primary end point (confirmed PSA response rate) will be presented as a proportion to be tested against a 1-sided alternative.

Patient demographics, clinical and treatment characteristics, and other study outcomes will be described using mean, SD and range, or median, IQR and range for continuous variables, frequencies, and percentages for categorical variables, and the Kaplan‒Meier method for time-to-event variables. The effect sizes and 95% CIs will be presented where possible.

Simon’s [18] 2-stage design will be used. The null hypothesis that the true response rate (serum PSA decline of more than 50%) is 20% will be tested against a 1-sided alternative. In the first stage, 24 patients will be accrued. If there are 5 or fewer responses in these 24 patients, this study will be stopped. Otherwise, 25 additional patients will be accrued for a total of 49. The null hypothesis will be rejected if 15 or more responses are observed in 49 patients. This design yields a type I error rate of 5% and a power of 90% when the true response rate is 40%.

To include 49 patients with mCRPC harboring HRR mutations, we must screen approximately 200 patients, assuming a 30% prevalence and tissue inadequacy of 20%. The type of HRR mutation will analyze subgroups. Regression models (using the Cox proportional hazards model) will be used for exploratory analyses.

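### No minimum baseline PSA is required for entry although the primary endpoint is a PSA fall of more than 50%, and the power margin for patients who cannot show it is thin

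*Protocol article*

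**What the plan says.** The Eligibility Criteria section of the protocol article introduces its inclusion list as conditions that must all be met. The list is detailed: testosterone, prior docetaxel or novel antiandrogen, a mutation, performance status, blood counts, liver enzymes and creatinine clearance. Disease status is "Documented current evidence of mCRPC, where metastatic status is defined as at least one documented metastatic lesion" on bone scan, CT or MRI. Neither a PSA level nor PSA progression appears.

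The abstract's Methods give the primary endpoint as the "proportion of patients with a reduction of serum prostate-specific antigen by more than 50% from enrollment". Statistical Methods calls it a confirmed PSA response rate and sets a one-sided test of a 20% null rate in two stages:

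- Stage 1 takes 24 patients, with this futility rule: "If there are 5 or fewer responses in these 24 patients, this study will be stopped".
- With 6 or more responses, 25 more are accrued, for 49 in total. The final rule reads: "The null hypothesis will be rejected if 15 or more responses are observed in 49 patients".

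The stated properties are 5% type I error, and 90% power at a true rate of 40%. The only allowance in the planned numbers is at screening, for mutation prevalence and inadequate tissue. Table 1 schedules serum PSA at baseline and at every cycle, but not at screening. The Results section reports 12 patients recruited.

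**The concern.** The go/no-go decision rests wholly on PSA, but nothing in the entry criteria checks that a patient's PSA can measurably halve. Metastatic castration-resistant disease is established here by imaging and testosterone, so a man with imaging-visible disease and very low PSA qualifies. If his baseline is at or near the quantification limit, a fall of more than 50% cannot be validly shown, whatever the drug does.

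Such a patient still takes one of the 24 or 49 places, because the rule is written on accrued patients and no evaluability or replacement rule is stated. If he is counted as a non-responder, he lowers the chance of passing both the 6-of-24 hurdle and the 15-of-49 hurdle. What is at stake is a false negative: an active, inexpensive treatment stopped early or judged inactive partly because the endpoint could not be observed in some patients.

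**Working it through.** **Inputs from Statistical Methods.** n1 = 24, continue with 6 or more responses; n2 = 25; N = 49, reject with 15 or more; null rate 20%, alternative 40%.

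**Input not in the article.** f, the share of enrolled patients whose baseline PSA is too low for a valid fall of more than 50%. It is an assumption, shown here from 0% to 20%.

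**Formula.** With X1 ~ Bin(24, p) and X2 ~ Bin(25, p),

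P(reject | p) = sum over x = 6 to 24 of P(X1 = x) × P(X2 ≥ 15 − x).

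**Step 1: reproduce the plan.**

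- p = 0.20: P(reject) = 0.0470, within the 5% stated. Probability of stopping at stage 1: 0.656.
- p = 0.40: P(reject) = 0.9133, against 90% stated. Probability of stopping at stage 1: 0.040.

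The stated design is correct. Its margin over 90% is 91.3 − 90 = 1.3 points.

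**Step 2: a share f cannot respond.** Suppose 40% holds among PSA-assessable patients and the others count as non-responders. The rate over all enrolled patients is then p = 0.40 × (1 − f).

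| f | p | Power |
|---|---|---|
| 0% | 0.400 | 91.3% |
| 1% | 0.396 | 90.5% |
| 2% | 0.392 | 89.5% |
| 5% | 0.380 | 86.3% |
| 10% | 0.360 | 79.5% |
| 15% | 0.340 | 70.7% |
| 20% | 0.320 | 60.2% |

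**Step 3: the same as a head count.** Fix k such patients among the 49, spread at random over the two stages. Power is 89.6% for k = 1, 87.7% for k = 2, 85.4% for k = 3 and 80.0% for k = 5. One patient (1/49 = 2.0%) is enough to use up the margin.

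**Step 4: type I error in the same model.** The null rate becomes 0.20 × (1 − f). Type I error falls to 3.1% at f = 5% and 2.0% at f = 10%. In this model the cost is in power alone.

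**The case against.** **The loss of power is not shown.** A reader might infer that the trial does not have its stated 90% power. The article does not support that. The claim is made for a true response rate of 40%, and at that rate exact power is 91.3%. No figure shows that any enrolled patient has an unassessable PSA. If 40% was meant as the rate over everyone accrued, which is a natural reading of a rule stated on 49 patients, there is no loss at all. This stands, so the figures for f above zero are conditional.

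**Low is not the same as unassessable.** A low but quantifiable PSA can fall by more than half. This also stands: the concern is limited to values at or near the quantification limit.

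**Type I error.** A reader might also infer that assay noise at low PSA would create false responses and inflate the type I error. The article gives no basis for any particular raised null rate. It also specifies a confirmed response, which works against a single noisy value being counted. No inflation is claimed.

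**Condensed article.** Handling of non-evaluable patients may well be set out in the full protocol or analysis plan, so its absence here is not a finding. Entry criteria are different. The article presents its list as the conditions to be met, and an analysis plan can decide how an unassessable patient is counted but cannot keep him out.

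**A floor part-way through.** It would give a mixed stage 1 population and slightly narrow the target population. That is true, but minor if enrolled patients stay in the count and the analysis is shown both ways. Merely stating how unassessable patients are counted would be lighter, but would still let them take places among the 49.

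**Conclusion.** The point holds in a limited, conditional form. Entry does not ensure that a patient can show the endpoint on which the whole decision rule rests, and the design has room for less than one such patient in 49 before power drops below 90%.

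The size depends on f, which is unknown: no effect at f = 0, about 1.8 points below the exact 91.3% at f = 2% (91.3 − 89.5), 5.0 points at 5% (91.3 − 86.3) and 11.8 points at 10% (91.3 − 79.5). These figures rest on two assumptions: that 40% describes PSA-assessable patients, and that unassessable patients count as non-responders. The plan's own power and type I error figures are not in error. The change is worth making because the gap is real and cheap to close, not because harm has been demonstrated.

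**What to change.** For all further patients, add one inclusion criterion: the baseline PSA already scheduled in Table 1, with its result available before cycle 1, is at or above a floor that the sponsor chooses and states, clearly above the assay's quantification limit.

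Keep every patient already enrolled in the 24 and 49 counts, so that the decision rule is unchanged and nobody is excluded after the fact. Add a sensitivity analysis of the primary endpoint that leaves out any patient whose baseline PSA is below the floor.

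**Cost.** One line of eligibility amendment, notified to the ethics committee and the registry as the article already provides for amendments. There is no new test. Slightly more patients must be screened, and the population is slightly narrower, which the report should state. With 12 of 49 recruited at the time of the article, the criterion could have covered up to 37 patients (49 − 12); the number is smaller the later it is introduced.

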### Interventions

Patients who agree to participate in this study will be tested for the presence of known deleterious mutations in the archived tumor tissue in genes involved directly or indirectly in HRR pathway: *BRCA1*, *BRCA2*, *ATM*, *BRIP1*, *BARD1*, *CDK12*, *CHEK1*, *CHEK2*, *FANCL*, *MSH2*, *PALB2*, *PPP2R2A*, *RAD51B*, *RAD51C*, *RAD51D*, and *RAD54L*.

Those found to have a pathogenic or likely pathogenic mutation in one of these genes will be treated with 3 weekly carboplatin. The dose will be calculated according to the estimated glomerular filtration rate determined by the Cockcroft-Gault equation and then administered at the area under the curve (5) with a dose capped at 750 mg per cycle. Chemotherapy will continue until progression (clinical, biochemical, or radiographic) or intolerable adverse events, whichever occurs earlier. If the patient misses a follow-up visit, this study’s team will contact the patient and reinforce adherence to this study.

The relevant concomitant care permitted or prohibited during the trial includes the following. Palliative radiation for patients who develop urgent local complications in previously documented disease sites. The ideal gap between palliative radiotherapy and the first dose of carboplatin would be at least one week, and there would be no capping dose of palliative therapy.

Continuation of protocol therapy, if medically appropriate, should be discussed with the principal investigator at the site. The following medications and treatments are permitted in this study: (1) rescue medications for nausea or vomiting, (2) antibiotics, and (3) bisphosphonates or denosumab.

Certain medications may interact negatively with carboplatin or interfere with its effectiveness. The medications that may have significant interactions or should generally be avoided with carboplatin:

Aminoglycoside antibiotics: these antibiotics, such as gentamicin or amikacin, may increase the risk of kidney damage when used concomitantly with carboplatin.Nonsteroidal anti-inflammatory drug: these drugs, including ibuprofen, naproxen, and aspirin, may increase the risk of bleeding or kidney damage when used concurrently with carboplatin.Live vaccines: live vaccines, such as the measles, mumps, rubella vaccine or varicella (chickenpox) vaccine, should generally be avoided during chemotherapy treatment, including carboplatin. These vaccines contain weakened live viruses that may pose a risk to immunocompromised individuals.Other nephrotoxic drugs: carboplatin can cause kidney toxicity, and combining it with other medications that have nephrotoxic effects, such as certain antibiotics or antifungal medications, may increase the risk of kidney damage.Anticoagulant medications: combining carboplatin with anticoagulants such as warfarin or heparin may increase the risk of bleeding. Close monitoring of blood clotting parameters is essential if these medications must be used together.Vaccines containing weakened or killed viruses or bacteria: while certain vaccines may be necessary for specific situations, it is important to discuss with a health care professional, as the timing and administration of vaccines should be carefully considered during chemotherapy treatment.

There are no medications or treatments that are specifically prohibited during this study.

All concomitant medications will be recorded at the time of registration.

Patients meeting either of the following criteria will discontinue this study’s treatment:

Permanent discontinuation of carboplatin by treating physician (unacceptable toxicity or progression of underlying cancer).The investigator determines that continuing this study’s treatment is not in the patient’s best interest.Occurrence of an exclusion criterion affecting patient safety.Concomitant treatment that is not permitted.Failure to comply with the protocol. Suppose a patient consistently fails to attend scheduled assessments in this study. In that case, the investigator will determine the reasons and document the circumstances in the medical records as thoroughly and accurately as possible.The patient declines subsequent treatment or withdraws consent.

Posttrial care would be administered based on the treating physician’s discretion. Patients will be followed up until disease progression. Data collected for this study comprise clinical characteristics obtained from hospital records and routine laboratory investigations, including but not limited to baseline demographics, outcome measures, treatment details, and adverse events.

